#### *6e ii. Medical record follow up*

Study subjects will be followed through review of routine medical records kept by the study site for a minimum of 10 months after the date of enrollment in the study for Track 1. This will allow all subjects who initiate ART within 3 months of study enrollment to reach the point at which the routine 6-month viral load is called for, with an additional month allowed for the viral load test to be completed. Subjects will continue to be followed until the final date of study data censoring, up to a maximum of 24 months after study enrollment.

In the study team's experience at other clinics in South Africa, a few patients who remain in care and make a clinic visit at the point at which the routine 6-month viral load test should be done do not have viral load results reported in their medical records. Should this happen, the subject's paper file and laboratory records at the site will be reviewed to confirm that no viral load test was done. If no test was done, a note will be placed in the subject's clinic file to remind clinic staff to ask the subject to provide a sample for viral load testing when she or he next comes to the clinic for routine medication pickup, which typically takes place every 2-3 months.

A blank consent form addendum will be placed in each Track 1 subject's clinic file to be used if the subject's care is being transferred to another clinic. The addendum will request consent to collect medical record data during the follow up period from the new clinic. It will be administered by study staff only if a transfer is being processed.

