#### 6f. Retrospective comparison group

As a second comparison group for Track 1, in addition to the standard group, data will be collected retrospectively for a sample of patients who were determined to be eligible for ART at Thuthukani Clinic during the 12 month period preceding the start of Track 1 enrollment. As there were no major changes to South African treatment guidelines during this period, the retrospective comparison group will provide information about uptake of ART before any study-related changes were made at the clinic.

Eligible subjects for the comparison group will be selected from the HIV counseling and testing (HCT) register maintained by the study clinic. This register indicates patients newly found to be ART-eligible from among those receiving an HIV test or a pre-ART CD4 count. Patients who became eligible over the period April 2012-March 2013 will be enrolled consecutively, starting with the later date and working backward in time until the target sample size is reached. Follow up data on pre-ART care, ART initiation, retention on ART, and viral suppression at 6 months will then be collected from the site's ART clinic files and electronic medical record system. Each subject will be followed for a 10-month period from the date at which the clinic determined that the patient was eligible for ART, corresponding to the 10-month primary outcome indicator for Track 1. A temporary identifier linking the HCT register record to the follow-up records will be created and retained until all data pertaining to an the individual study subject have been collected and quality checked. Because all data will already exist at the time the sample is selected, the identifier will serve only to link records at the same site, and all records can be accessed on site, at the same time, the identifier for any individual subject will be kept for a very short period.

Procedures for collecting data for this group will be similar to those used for the Track 2 retrospective group, described below. The study will have no direct interaction with subjects in this group.

## 7. Procedures for Track 2

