## 10. Sample Size

Track 1: In a recent study we conducted in Johannesburg, we found that among patients eligible for ART, 46% initiated ART within 16 weeks of eligibility. In an analysis of data from the same Johannesburg site, we estimated that among more than 3000 patients initiated on ART in 2010 and 2011 who remained in care, 77% were virally suppressed at the routine 6-month viral load. We would thus expect approximately  $0.46 \times 0.77 = 35\%$  of those eligible to have both started treatment and be virally suppressed by the 6-month viral load. For our study site we conservatively estimate that 50% of those eligible for treatment in the standard group will be suppressed by 10 months after their HIV test. We anticipate that the rapid initiation strategy will increase the proportion suppressed to 70%.

For our primary analysis, using an  $\alpha$  of 0.05, power of 90%, 1:1 randomization, and an uncorrected Fisher's exact test, we would need to enroll 124 HIV positive ART-eligible subjects per group (248 total). We expect 70% of all HIV-positive patients to be eligible for ART under current South African guidelines on the day they test positive for HIV or make their first HIV care visit, based on results from published studies in South Africa. Therefore to reach 124 subjects per arm who are treatment eligible on the day of testing we will need to consent 177 subjects per group (354 total). To allow stratification in the analysis by sex and by site, we will consent up to 300 per group (600 total) to have adequate power. We will enroll in the study up to 67% of this total (enrollment=400).

The sample size for the Track 1 retrospective comparison group will be 120. This group will be limited to patients already found to be eligible for ART at one of the two study sites (Thuthukani). They will be compared with each of the two randomized prospective groups (rapid and standard). We expect that Thuthukani will account for approximately 60% of total prospective enrollment of 400, or 120 in each of the randomized prospective groups. We will thus aim to enroll the same the number of subjects into the retrospective comparison group as in each prospective group.

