## 11. Outcomes and Data Analysis

### 11a. Outcomes

#### 11a i. Primary outcome

Track 1: The primary outcome for Track 1 is the proportion of subjects in each group alive, in care and virally suppressed at the routine six-month on ART monitoring visit within 10 months of a positive HIV test or initial HIV care visit if previously diagnosed. The analysis period will start at study enrollment and continue through the earlier of the patient's six-month viral load or 10 months after the patient's HIV test.

Under South African treatment guidelines, all ART patients have a monitoring viral load done at six months after ART initiation. We will use this measure to assess our primary outcome. In order to create comparable follow-up time in both groups and to allow all subjects enough follow up time to have a six-month viral load, for the primary outcome analysis we will consider all ART-eligible patients who do not have a six-month viral load for any reason within 10 months of study enrollment to be failures. Viral suppression will be defined as <50 copies/ml. Patients in the rapid group who do not initiate treatment on the day of their HIV test will remain in the intervention arm for analysis (i.e. intention to treat).

Our primary outcome will be measured 10 months after study enrollment because the first 6 months on ART is the time when patients are most likely to be lost or die. At the 10-month point after study enrolment, all subjects who started ART within 3 months of enrolment will have had the opportunity for at least 6 months of exposure to treatment and allow an additional month for subjects to return to the clinic for their routine 6-month viral load test. If rapid initiation triggers a higher rate of loss to follow up after starting treatment, the impact is likely to be evident within six months of initiation. Six months of ART is also sufficient to achieve viral suppression in the vast majority of patients. In an analysis of >13,000 patients who initiated ART at a large clinic in Johannesburg, 75-80% of all patients were virally suppressed after a median (IQR) of 3.9 (3.7-5.0) months. We would thus expect at least 80% of patients to reach viral suppression by 6 months on ART.

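### Six-month viral loads are ascertained less fully in the Track 1 retrospective group than in the randomized arms, which slightly favours the prospective arms in the historical comparison

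*Protocol*

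**What the plan says.** For prospective Track 1 subjects, Protocol section 6e ii anticipates "a few patients who remain in care and make a clinic visit at the point at which the routine 6-month viral load test should be" carried out, yet have no result in the record. In that case "the subject's paper file and laboratory records at the site will be reviewed to confirm that no viral load test was done". If none was done, "a note will be placed in the subject's clinic file to remind clinic staff to ask the subject to provide a sample" at the next routine medication pickup, which that section puts at typically every 2–3 months.

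For the retrospective group, section 6f says that "viral suppression at 6 months will then be collected from the site's ART clinic files and electronic medical record system". It describes a pure record review with no contact: "Because all data will already exist at the time the sample is selected", the linking identifier is kept only briefly. Follow-up is 10 months from the date eligibility was determined, and 6f ties that period to the Track 1 primary outcome indicator. It describes the group as informative about ART uptake before the study changed anything at the clinic.

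Section 11a i counts ART-eligible patients "who do not have a six-month viral load for any reason within 10 months of study enrollment to be failures". Section 10 sets the retrospective group at 120 and says: "They will be compared with each of the two randomized prospective groups (rapid and standard").

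**The concern.** The retrospective group is read against the randomized arms on an indicator matched to the primary outcome, but the two sides do not have the same chance of a viral load being found. A patient who is in care and suppressed, but whose result never reached the clinic file or electronic record, can be rescued in a prospective arm by the laboratory search, or by a late sample after the note. The same patient in the retrospective group has neither route.

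Where a missing result is scored as failure, a search or prompt can only turn a failure into a success. The error therefore has one direction, and enrolling more subjects would not reduce it. At stake is how the historical comparison is read: part of any gap between the standard arm and the retrospective group, or of the gain of the rapid arm over it, could reflect more complete measurement. The note is also itself a study-related change at the clinic, and the retrospective group is meant to show the clinic before any such change.

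**Working it through.** **The plan's own figures.** With 50% versus 70%, two-sided alpha 0.05 and 90% power, the pooled-variance formula without continuity correction is

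n = [1.96 × √(2 × 0.6 × 0.4) + 1.2816 × √(0.5 × 0.5 + 0.7 × 0.3)]² / 0.2² = (1.358 + 0.869)² / 0.04 ≈ 124 per group,

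as section 10 states. The retrospective size also reproduces: 400 × 0.60 / 2 = 120. Neither figure is disputed.

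**Ascertainment side by side.**

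| Step when the six-month viral load is missing | Randomized arms (6e ii) | Retrospective group (6f, 8e) |
|---|---|---|
| Paper clinic file | yes | yes |
| Laboratory records at the site | yes | not stated |
| Note prompting a new sample | yes | impossible |

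The paper file is common to both sides. The difference is the laboratory search and the note.

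**Size.** Let p be the true success rate, m the share of true successes with no viral load in the file or electronic record, and r the share of those recovered within 10 months by search or note. If missing counts as failure in both groups:

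- recorded rate, prospective arm = p × (1 − m × (1 − r))
- recorded rate, retrospective group = p × (1 − m)
- spurious gap = p × m × r

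Inputs: p = 0.50, the control rate in section 10, taken as equal in both groups; n = 120 per group. The protocol gives no value for m or r, so both are assumptions. The standard error of the difference is √(2 × 0.5 × 0.5 / 120) = 6.5 points. False-positive rates are exact binomial for the uncorrected two-proportion test at two-sided 0.05; with no gap the rate is 4.5%.

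| m | Gap, r = 0.5 | Gap, r = 0.8 | False p < 0.05 |
|---|---|---|---|
| 2% | 0.5 points | 0.8 points | 4.6–4.7% |
| 5% | 1.25 points | 2.0 points | 5.0–5.6% |
| 10% | 2.5 points | 4.0 points | 6.3–8.9% |
| 20% | 5.0 points | 8.0 points | 12–23% |

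For rapid (70%) versus retrospective (50%) at m = 10% and r = 0.8, the recorded gap is 0.7 × 0.98 − 0.5 × 0.90 = 23.6 points. It would be 20 if every test were seen, and 0.2 × 0.90 = 18 if neither side were repaired.

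**Timing of the note.** A prompted sample counts only if it falls inside 10 months. A subject starting ART at month 3 is due for the viral load at month 9; a pickup 2–3 months later falls at months 11–12, too late. With the 42-day average interval quoted in section 3b (about 1.4 months), the test is due at month 7.4 and the prompted sample falls at months 9.4–10.4. In the standard arm the note may therefore recover few results, and r may lie below the range shown.

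**The case against.** Four objections carry weight.

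- **A laboratory look-up is not barred.** Section 6f says all records can be reached on site, 8e adds paper records and registers and lists viral loads among the fields to be abstracted, 8f ii keeps laboratory printouts at the site, and 12e gives its sources as examples. That is fair: the restriction is inferred from the sources listed. But no section sets the missing-result search for this group, and the note would still differ even if laboratory records were consulted in practice.
- **The failure rule is written for the randomized arms.** Section 11a i counts time from study enrollment and speaks of both groups. Applying it to the retrospective group is an inference from the matching 10-month indicator in 6f. This stands as a condition on the conclusion.
- **The stated purpose is uptake of ART**, which does not depend on viral load ascertainment. This also stands. But 6f collects suppression as well, and no section confines the comparison to uptake.
- **The comparison is non-randomized anyway.** Consent, the exclusion of patients intending to seek care elsewhere, and calendar time also separate the groups, so equal ascertainment would not make the comparison unconfounded. True, but this particular difference is avoidable at little cost.

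A reader might go further and infer that the historical comparison will show a study effect where none exists. The documents do not support that: they speak of only a few such patients, and at m = 2–5% the false-positive rate stays near nominal. A reader might also infer a bias in rapid versus standard. This point makes no such claim: 6e ii applies the same search and note to both randomized arms.

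**Conclusion.** The difference in ascertainment is real and, if missing counts as failure in the retrospective group, it can only favour the prospective arms. Its size cannot be known from the protocol and is probably small: about 0.5–2 points if 2–5% of true successes lack a result and 50–80% of those are recovered. It reaches 2.5–8 points only if 10–20% are missing. These figures rest on an assumed equal true success rate of 50% and on assumed m and r. The point affects a supplementary, non-randomized comparison. It is a minor, cheap improvement.

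**What to change.** 1. In section 6f, apply the laboratory-record search of 6e ii to every retrospective subject with no viral load in the clinic file or electronic record.
2. For prospective Track 1 subjects, record whether the viral load was obtained after a study note. Keep those results in the main historical comparison of suppression, and report the comparison also with them counted as missing, as a sensitivity analysis. Discarding valid in-window results in the only analysis would be hard to defend.
3. Lead the historical comparison with ART uptake, the purpose that 6f already states.

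The cost is a look-up for part of 120 subjects, one yes/no field at data collection, and a few lines of protocol text. The flag must be captured at collection, since note-prompted results may not be separable later. Sample size and the randomized comparison are unchanged.

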- Nearly half of those who are eligible for ART (49%) do not return to obtain their CD4 count results within 3 months, and are thus not aware of their need for treatment; and
- Even among those who do receive their CD4 count results and are eligible or fast-tracked for ART (CD4  $\leq$  250) fewer than half (46%) initiate ART within four months of HIV testing.

This problem is likely to be even worse among patients who obtain an HIV test from a mobile or stand-alone HIV counseling and testing site, and thus must be referred elsewhere for a CD4 count and other services. South Africa's recent raising of the treatment eligibility threshold to CD4  $\leq$  350 is likely to exacerbate this problem further, as more asymptomatic patients become eligible.

Failure to initiate ART promptly is also an acute problem amongst pregnant women who are diagnosed with HIV during antenatal care. A study in Cape Town, South Africa found that only half (51%) of pregnant women who were eligible for full HAART (three drug treatment regimen rather than PMTCT regimen) under previous guidelines (CD4 count  $< 200$  cells/mm^3) initiated treatment prior to delivery, increasing the risk both to themselves and to their infants.

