#### *Inclusion criteria:*

- Adult patients ( $\geq 18$  years)
- For Track 1, tested HIV-positive at study site's outpatient testing service on day of study enrollment or previously tested HIV-positive but providing a blood sample for a CD4 count or receiving CD4 count test result on day of study enrollment
- Eligible for antiretroviral therapy under prevailing South African guidelines\*

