#### 8e. Medical record data

Most data for the study will be collected from the site's routinely maintained electronic medical records, which are maintained in an information system called Therapy Edge-HIV™. Records in this information system are typically only created once a patient starts ART. Paper-based medical records kept by the site will therefore be used to supplement the electronic medical record system as needed. The fields to be collected are listed below.

*To be used to link electronic and paper-based records to study identification number only:*

- Electronic medical record system number
- Clinic file numbers
- National ID number
- Name
- Date of birth

*All subjects at baseline (ART initiation):*

- Date of positive HIV test (if available)
- Sex
- Age in years
- Weight and height or BMI
- Date treatment eligibility determined, if reported
- Date and result of eligibility-determining CD4 count
- Date and result of TB symptom screen
- Date, type, and result of TB test(s)
- TB treatment, if relevant
- WHO stage and clinical conditions
- Date ART initiated (first dose of drugs dispensed)
- First-line regimen prescribed

*For all clinic visits for duration of study follow up, including initial visit and pre-ART visits (to be used to estimate resource utilization):*

- Date of visit
- Primary reason for visit (e.g. scheduled medical visit, medication pickup, unscheduled medical visit)
- Types of professionals seen (e.g. nurse, doctor, pharmacy assistant, counselor)
- Group and individual sessions attended (e.g. wellness course, adherence education)
- Numbers and types of all lab tests conducted (including CD4 counts and viral loads)
- Other procedures (e.g. x-rays) performed

- Medications prescribed and dispensed (ARV and non-ARV)
- Admissions for inpatient care since previous visit, if recorded
- Details of inpatient care received (facility, number of days, medications, lab tests, etc.) if recorded

*At interim and final dates of data censoring:*

- Date and result of most recent viral load test
- Status at clinic (in care / died / transferred to another site / stopped care / lost to follow up, defined as > 1 month late for last medication pickup)
- New or recurring HIV-related conditions
- Date and cause of death if applicable
- Date and result of most recent CD4 count

*Track 2 subjects only (pregnant women):*

- Gestational age at diagnosis or first ANC visit for current pregnancy if previously diagnosed
- Prior exposure to PMTCT

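### The retrospective group's 10 months start at the clinic's eligibility determination, which is later than the Track 1 start it is said to match for patients enrolled at HIV test or CD4 draw

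*Protocol*

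**What the plan says.** Section 6f (Retrospective comparison group) draws patients from the clinic's HIV counseling and testing register, which shows those newly found eligible for ART. It follows each for a "10-month period from the date at which the clinic determined that the patient was eligible for ART" and describes this as "corresponding to the 10-month primary outcome indicator for Track 1".

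Section 11a i (Primary outcome) defines that indicator as suppression at the six-month visit "within 10 months of a positive HIV test or initial HIV care visit if previously diagnosed". Other sentences in the same section use study enrollment. One sets the window for analysis: "The analysis period will start at study enrollment and continue through the earlier of the patient's six-month viral load or 10 months after the patient's" (it closes by naming the test). In the other, patients are failures if they "do not have a six-month viral load for any reason within 10 months of study enrollment to be failures".

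The inclusion criteria in section 5c place Track 1 enrollment on the day of a positive HIV test or, for patients diagnosed earlier, on the day they are "providing a blood sample for a CD4 count or receiving CD4 count test result on day of study enrollment".

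Section 10 sets the retrospective group at 120 patients and commits to comparing it with each randomized group.

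**The concern.** The two windows have the same length but different starting points. A patient enrolled in Track 1 at the test or blood draw starts the clock before anyone knows whether he or she is eligible. A historical patient starts it once the clinic has decided. The delay in between is part of the process that rapid initiation is meant to shorten, and it is charged to the randomized groups but not to the historical one.

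Extra time matters because the outcome counts a missing six-month viral load as failure, and section 6e ii builds the 10 months as three months to start ART, six on ART and one for the test. A later clock raises historical success. The rapid group would then look less effective against history, and the standard group would look somewhat worse than usual care. The second point bears directly on the group's stated purpose, which is to show uptake before any study-related change at the clinic.

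A second effect may act in the same direction. If eligibility enters the register only when the patient comes back for the result, eligible patients who never came back are not in the historical sample. In the standard group, section 6d i has the study team monitor laboratory results to find eligible subjects.

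**Working it through.** **The plan's own figures.** For 50% against 70%, two-sided alpha 0.05, power 90% and no continuity correction, the sample size is 124.0 per group, as stated in section 10. The retrospective 120 is not a power result: 0.60 × 400 / 2 = 120. Neither figure depends on the start date.

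**Inputs.**
- Lag from blood draw to eligibility: results in about one week (section 6d i); 2 days to 4 weeks for a completed baseline CD4 count (section 3b).
- Latest useful ART start: 3 months, taken as 91 days (section 6e ii).
- 46% of eligible patients start within 16 weeks (112 days), and 77% of those in care are suppressed at the six-month viral load (section 10). 0.46 × 0.77 = 0.354.
- Mean time to start among those starting within 16 weeks: 42 days (section 3b).
- Assumption, not in the protocol: times to start follow an exponential distribution truncated at 112 days. A mean of 42 days gives a rate of 0.0139 per day.

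**Extra time in the window.** With 30.44 days per month, the 3 months available to start ART, counted from the draw, become:

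| Lag | Months to start ART | Increase |
|---|---|---|
| 2 days | 3.07 | 2% |
| 7 days | 3.23 | 8% |
| 14 days | 3.46 | 15% |
| 28 days | 3.92 | 31% |

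**Effect on the success rate.** The share of starters who start by day t is F(t) = (1 − exp(−0.0139 t)) / (1 − exp(−0.0139 × 112)). Success is 0.354 × F(t).

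| Lag | t (days) | F(t) | Success | Gain (points) |
|---|---|---|---|---|
| none | 91 | 0.910 | 32.2% | – |
| 2 days | 93 | 0.919 | 32.6% | 0.3 |
| 7 days | 98 | 0.943 | 33.4% | 1.2 |
| 14 days | 105 | 0.973 | 34.5% | 2.2 |
| 28 days | capped at 112 | 1.000 | 35.4% | 3.2 |

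The last row is capped because the source data stop at 16 weeks; 91 + 28 = 119 days lies beyond them.

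**Against sampling error.** At 120 per group and a rate near 50%, the standard error of a difference is sqrt(2 × 0.25 / 120) = 0.0645, or 6.5 points. One week's shift is about 0.2 standard errors; the four-week figure is about 0.5.

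**Omitted losses, conditional.** If a share q of eligible patients were lost before the register recorded them, and none would have succeeded, a true rate p would appear as p / (1 − q). With p = 50%, assumed values of q of 5%, 10% and 20% give 53%, 56% and 63%. The protocol supplies no q for this clinic, so these values show the form of the effect and do not estimate it.

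**The case against.** The strongest reply is that section 11a i also counts the failure rule from study enrollment, and that sections 6b vi, 6c iii and 6d i describe subjects as enrolled only once eligibility is confirmed. On that reading, enrollment and eligibility determination do coincide, and section 6f is right. This shows that Track 1's own time zero is worded two ways. It does not remove the mismatch: the outcome definition itself runs from the test or first care visit, and the inclusion criteria put enrollment on the day of test, draw or result.

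Second, some Track 1 patients enter on the day they receive a CD4 result. For them eligibility and enrollment fall together and there is no shift. This stands and limits the point to patients enrolled at test or draw.

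Third, a reader might infer large omitted losses from section 3a, where nearly half of eligible patients "do not return to obtain their CD4 count results within 3 months". The documents do not support that step. The figure comes from another Johannesburg facility and concerns patients' return, not what the Thuthukani register records. Section 6f dates eligibility by the clinic's determination and does not require that the patient was told. If the register takes eligibility from the laboratory result, few losses are omitted. The contrast with the standard group is also less sharp than it may look, since section 8f ii has standard-group eligibility checked from the site's paper files as well.

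Finally, this is a second comparator and appears in none of the listed objectives. That is right, but section 10 promises the comparison and section 6f asserts an equivalence that does not hold.

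**Conclusion.** The mismatch is real and modest. For Track 1 patients enrolled at test or draw, the historical group gains about one week, with a range of 2 days to 4 weeks. That is worth roughly 1 to 3 points of success in its favour at lags of one to four weeks, under the protocol's initiation and suppression figures and the assumed exponential time to start. It applies to the comparisons with both randomized groups. It does not touch the randomized primary comparison or the sample size of 124 per group.

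The omission of patients who never returned is possible but not established. It depends on how the register records eligibility, which the protocol does not say. Its direction would be the same and its size is unknown. A claim that it could absorb most of the planned 20-point difference would rest on loss shares that nothing in the protocol anchors, and that difference was planned for the randomized comparison.

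**What to change.** 1. In section 11a i, state one time zero for Track 1: the day of the qualifying HIV test, CD4 draw or result visit. Use it in the outcome definition, the analysis period and the failure rule.
2. In section 6f, start the retrospective 10 months at the equivalent date: the positive HIV test, or the CD4 blood draw for patients diagnosed earlier. Select patients consecutively by that date.
3. Include every register patient whose CD4 result meets the eligibility criterion, whether or not a return visit is recorded. Count those without a six-month viral load in the window as failures. State how the register records eligibility.
4. Repeat the historical comparison restricted to Track 1 patients enrolled at test or draw, because a draw date does not match those enrolled on receiving a result. The entry route must be held for each Track 1 subject.

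The cost is small. Section 8e already lists the HIV test date and the date of the eligibility-determining CD4 count. The HIV test date is qualified as collected where available, so some will be missing, but the present anchor has the same weakness: "Date treatment eligibility determined, if reported". Some dates or CD4 results will need a record look-up, and the historical success rate may come out slightly lower. No sample size changes.
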